## Abstract

**Background:**

Patient self-monitoring via mobile phones during psychotherapy can enhance and provide an overview of psychotherapeutic progress by graphically displaying current and previous symptom scores, providing feedback to the patient, delivering psychoeducative material, and providing timely data to the therapist or treatment team.

**Objective:**

This study will aim to assess the effects of using a mobile phone to self-monitor symptoms and acquire coping skills instead of using pen and paper during psychotherapy in patients with borderline personality disorder (BPD). Dialectical behavior therapy will be performed to treat BPD. The primary outcome is the mean time needed to learn coping skills directed at emotion regulation; the secondary outcome is changes in the BPD symptom score as measured by the Zanarini Rating Scale for Borderline Personality Disorder.

**Methods:**

This study is a pragmatic, multicenter randomized controlled trial. Participants were recruited through five public general psychiatric outpatient treatment facilities in Denmark. Patients are randomly assigned, on a 1:1 basis, to either the mobile phone condition (using the Monsenso mDiary mobile app) or pen-and-paper condition. Patients will complete several self-report questionnaires on symptom severity; assessments by trained raters on BPD severity will be performed as well. Survival analysis with a shared frailty model will be used to assess the primary outcome.

**Results:**

Recruitment began in June 2017 and was completed in February 2019 after 80 participants were recruited. The study ended in February 2020. It is expected that the benefits of mobile phone–based self-report compared to the pen-and-paper method will be demonstrated for skill learning speed and registration compliance. To our knowledge, this is the first trial exploring the impact of cloud-based mobile registration in BPD treatment.

**Conclusions:**

This trial will report on the effectiveness of mobile phone–based self-monitoring during psychiatric treatment. It has the potential to contribute to evidence-based clinical practice since apps are already in use clinically.

**Trial Registration:**

ClinicalTrials.gov NCT03191565; https://clinicaltrials.gov/ct2/show/NCT03191565

**International Registered Report Identifier (IRRID):**

DERR1-10.2196/17737

## Introduction

The prevalence of borderline personality disorder (BPD) in the general Scandinavian population is estimated to be 1% to 5% [1,2]. The consensus is that approximately 1.5% of the western population meets the criteria for BPD [2]. The prevalence in clinical populations is considerably higher and is estimated to be around 28%, ranging between 9.3%-46.3% of patients, according to current studies [3,4]. In Scandinavia, the mortality risk of patients with a mental disorder is 2-3 times higher than in the general population [5]. The suicide rate for BPD patients is estimated to be between 8%-10%, almost 50 times higher than in the general population [6].

BPD is characterized by instability in emotion and mood, interpersonal relationships, self-image and identity, and impulse and behavioral control [7]. A 3-factor structure has been found empirically and supported by confirmatory factor analysis; the factors were disturbed relatedness, behavioral dysregulation, and affective dysregulation [8]. In dialectical behavioral therapy (DBT), these problems are viewed as skill deficits that result from problems with regulating emotion [9].

DBT has demonstrated effectiveness and is regarded as one of the most well-researched, evidence-based treatments for BPD [10-12]. The treatment includes the “five functions” of DBT—skill acquisition, skill generalization, motivation to implement new and skillful behaviors, interventions in the social and family environment to allow for treatment progress, and a consultation team to facilitate skillful treatment delivery and reduced burnout among therapists. Thus, the central focus is on learning skills that target self-management through mindfulness skills, healthier relationships with family and peers through interpersonal skills, handling of severe emotional dysregulation through distress tolerance and crisis survival skills, and proactive, effective management of emotional reactions through emotion regulation skills [13]. All of these types of skills are typically trained in a group format, and motivation and implementation are the foci of individual therapy.

### Self-Monitoring During Therapy

Self-monitoring of skill use and accompanying changes in suicidality, self-harm, and emotional reactivity during DBT therapy have traditionally been done using paper-based diaries. Technological advances in mobile apps have made new modes of self-monitoring possible and may reduce the burden on patients, increase data quality, and generate new opportunities for registration [14,15], like enhanced overview [16], ecological momentary assessment [17], and research investigating predictors of the course of therapy to facilitate future development [18,19]. However, monitoring of patients with BPD on mobile phone diary apps should be explored and evaluated before they are implemented in clinical practice in a broader sense [20].

Recent studies on pain management have demonstrated good usability in using digital self-monitoring [21,22]. Furthermore, studies using digital diaries in the treatment of bipolar disorder [19,23] in pain and weight management, sleep, and chemotherapy have all shown promising results [24-27]. Apps specifically targeting emotional awareness, posttraumatic stress reduction, and suicidality in borderline personality disorder are currently being investigated [28-30]. DBT skills have been shown to mediate improvements in BPD defining behaviors [31-35]. DBT-related apps supported by scientific inquiry have been developed at Rutgers University (Pocket Skills) [36] and the University of Washington (DBT Coach) [37]. These apps have been reported to show promise and acceptability among users. They are specialized in training and coaching skills, include diary card data as a secondary feature, and are self-contained within the app. The end users in the Pocket Skills usability study requested enhanced visualization of diary card scores as well as aggregated scores.

In this study, we used the mDiary app to fill this gap in research as well as to eliminate conventional paper diary cards through new technology. The mDiary app has a cloud-based self-monitoring system that is sharable with a therapist in real time. To our knowledge, this app is the first BPD-focused mobile app to provide sharable self-monitoring.

The Monsenso system used in our study is a modified version of the system used in the 2009 MONARCA trial, which tested a system aimed at self-monitoring bipolar disorder [38]. The MONARCA-project was developed at the IT University of Copenhagen as part of a PhD project, and a modified version of the MONARCA software is now sold by the Danish company Monsenso. The Svendborg DBT Unit modified the Monsenso mobile app to suit the needs of patients with BPD; modifications were made to the DBT treatment skills-training modules and psychoeducation content, and an enhanced therapist overview screen was added to the Monsenso system. Patients were involved in the design of the solution. A consistent focus on emotion regulation, the monitoring of progress in skills training, and compliance with standard DBT treatment [39] were prioritized in the mDiary app. The resulting solution was tested in a pilot feasibility study and showed adequate usability among patients and therapists [40].

### Objectives

The objectives of the current study are to evaluate (a) if patients randomized to use the Monsenso mobile app learn DBT skills faster compared to patients randomized to the pen-and-paper version; (b) if patients using the app report higher reductions in BPD criteria; (c) if registration compliance improves with a mobile phone, and (d) if use of the mobile app is cost-effective compared to the pen-and-paper version. We expect that use of a mobile phone–based digital diary will reduce the time it takes for patients to acquire DBT skills, improve therapy outcomes, and be cost-effective.

## Methods

### Study Design

The study is a pragmatic 2-arm, multicenter, open-label, evaluator-blind, superiority randomized controlled trial (RCT), with the active arm being self-registration done through the Monsenso mDiary mobile app and the control arm being self-report done by pen-and-paper diary cards. Figure 1 presents the CONSORT (Consolidated Standards of Reporting Trials) flowchart and details on patient inclusion, and Table 1 provides an overview of the study.

**Figure 1 figure1:**
[figure not shown]
CONSORT (Consolidated Standards of Reporting Trials) flowchart. DBT: dialectical behavioral therapy; DERS: Difficulties in Emotion Regulation Scale; BSL-23: Borderline Symptom List; ZAN-BPD: Zanarini Rating Scale for Borderline Personality Disorder.

**Table 1 table1:** Items from the trial registration data set.

Data category	Information
Primary registry and trial identifier	ClinicalTrials.gov (NCT03191565)
Date of registration in primary registry	June 19, 2017
Secondary identification numbers	S-20160085 5159-00002B 2008-58-0035
Source of monetary or material support and sponsor	The Danish National Innovation Fund (grant number 5159-00002B)
Contact for public queries	Centre for Telepsychiatry, Odense, Denmark
Contact for scientific queries	Research Unit for Telepsychiatry and E-mental Health, Odense, Denmark
Public title	Differences in electronic and paper-based self-monitoring in borderline personality disorder: which is most effective?
Scientific title	Daily Self-Monitoring of Symptoms and Skills Learning in Patients With Borderline Personality Disorder Through a Mobile Phone App: Protocol for a Pragmatic Randomized Controlled Trial
Countries of recruitment	Denmark
Health condition(s) or problem(s) studied	Borderline personality disorder
Intervention(s)	Active comparator: self-monitoring by mobile phone Placebo comparator: *self-monitoring by pen and paper*
Key inclusion and exclusion criteria	Inclusion criteria: adult patient (≥18 years), emotionally unstable personality disorder (ie, ICD-10-CM^a^ diagnosis code: F60.3); referred to psychiatric treatment (ie, DBT^b^ psychotherapy); suicide attempt within the last 3 years Exclusion criteria: patients with schizophrenic spectrum disorders and bipolar disorder; substance abuse as primary problem (no desire to stop); intellectual problems (ie, IQ below 70)
Study type	Interventional Allocation: pragmatic, 2-arm, multicenter, open-label, evaluator-blind randomized controlled trial Active arm: self-registration with the Monsenso mobile app; control arm: self-report by pen-and-paper diary cards Primary purpose: intervention Phase III
Date of first enrollment	June 2017
Target sample size	80
Recruitment status	Active, not recruiting
Primary outcome(s)	Mean number of days required to learn a new DBT skill (time frame: 1 year)
Key secondary outcomes	Borderline severity (ZAN-BPD^c^), ability to regulate emotion (DERS^d^), compliance filling out diary cards

^a^ICD-10-CM: International Classification of Diseases, 10th Revision, Clinical Modification.

^b^DBT: dialectical behavior therapy.

^c^ZAN-BPD: Zanarini Rating Scale for Borderline Personality Disorder.

^d^DERS: Difficulties in Emotion Regulation Scale.

### Recruitment

Patients in the DBT treatment group for BDP and related problems will be recruited from five psychiatric outpatient units treating BDP (ie, Svendborg, Haderslev, Vejle, Silkeborg, and Glostrup) between August 2017 to December 2019. All sites have comprehensive DBT programs that have functioned as standard DBT programs for more than 7 years and include all five modes of DBT (ie, weekly consultation team; skills training groups; individual therapy, along with telephone coaching available outside of therapy sessions; and help structuring clients’ social and family environments if relevant [41]).

All patients will be informed orally and in writing about the research project. Consent for participation will be obtained not from the therapist of the patient but from an unbiased research assessor from the mDiary team. Patients were involved in designing the mDiary app.

Patients will be included in the study provided they fulfill all of the inclusion criteria and none of the exclusion criteria; they must also provide written informed consent, which will be collected by the therapists. Inclusion criteria are as follows: aged 18 years or older; a primary diagnosis of Emotionally Unstable Personality Disorder (F60.3 according to ICD-10-CM [International Classification of Diseases, 10th Revision, Clinical Modification] criteria) and diagnosed by a specialist in psychiatry (referred to as BPD here, the more common diagnostic label); referral for psychiatric treatment at the DBT treatment sites involved in the study; willingness to sign a commitment contract for DBT treatment; having had problems with self-harm or suicidal behavior within the last 3 years. Self-harm is defined as any form of self-inflicted tissue damage, excluding superficial scratching. Comorbid depression, anxiety, PTSD, antisocial traits or micro-psychotic episodes are not exclusion criteria as long as BPD is primary diagnosis. The above criteria will be screened through the Symptom Checklist-90-R (SCL-90-R) questionnaire subscores as well as targeted questions during the assessment interview. Patients with secondary substance use will be included if they agree to work on reducing their abuse.

The exclusion criteria are as follows: any diagnosis of schizophrenic spectrum disorders (any type of schizophrenic disorder or schizotypal personality disorder); any diagnosis involving bipolar disorder or a comorbid diagnosis of substance abuse disorder without a wish to change the associated behavior. The exclusion criteria will be checked in the electronic patient journal and through structured interviews during the intake procedure. Patients with intellectual problems comparable to an IQ below 70 will be excluded. Screening for intellectual disability will be done with the Danish Adult Reading Test (DART) [42]. Lack of a mobile phone or participation in other concomitant psychotherapy will also be reasons for exclusion.

### Statistical Analysis

The primary endpoint is the skills learning rate—the amount of time (in days) taken to learn a new skill (ie, progress from “started learning the skill” to “have learned the skill”). Patients assess and switch status using a button on the mobile phone app when they consider the skill is of use to them; at this time, the skill is considered learned, which will then be discussed and confirmed with the therapist during the preceding session.

The secondary endpoints are (a) BDP symptoms, including the ability to regulate emotion, will be evaluated with the interview-based ZAN-BPD; (b) percentage of completed diary questions, measured as a day with an entry in the mDiary app or in the paper-based diary; (c) quality of life measured by the EuroQoL five-dimension, five-level (EQ-5D-5 L) instrument; and (d) depression measured with the Patient Health Questionnaire (PHQ-9).

### Power

We are planning a study of 80 patients with equal allocation to each arm, an accrual interval of 360 days, and an additional follow-up of 360 days. The sample size of 80 patients is a realistic recruitment goal for the given timeframe. To our knowledge, no studies have previously investigated DBT skill acquisition time through the use of mobile phones. Based on pilot data and relevant noticeable clinical differences, it is estimated that the mean time to learn a DBT skill will be 1.5 month (44 days) for mobile phone registration versus 2 months (60 days) for the control condition. Using an alpha of .05 and a power of .90, we will need 437 events of learned skills in total to reject the null hypothesis. With an expected attrition rate during follow-up of 20%, each remaining patient (n=64 will on average need to generate 7 learned skills. A very cautious estimate would be that half of the patients (32 patients) will learn half of the skills (16 skills) during one year of therapy. This would generate 512 events, meaning that an inclusion of 80 patients will be able to generate sufficient power. A more realistic expectation is that 75% of the patients following protocol will learn 75% of the skills, which will generate 1188 events and will leave ample room to adjust for shared frailty. It is estimated that at least 15,000 episodes of a specific skill use will contribute to the survival analysis. The power analysis was performed using R statistical software and gsDesign. The power calculation is based on the log-rank test [43].

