### Statistical Analysis

All analyses will be conducted according to the intention-to-treat principle. Comparison between the active and control conditions on the primary endpoint will be performed by means of survival curves, as time-to-event models analyzed by Cox proportional hazards regression models with multiple events per patient. Significance tests are based on a frailty mixed effects approach [55]. Since missing data is not expected to be missing randomly, data will be modelled with multiple imputations, if missing data is to be included.

The level of dependence or heterogeneity among patterns of skill acquisition speed within the same site will also be explored by the intracluster correlation coefficient (ICC) [56]. Apart from intervention type (mobile phone or paper), treatment site, intellectual ability (DART score), level of BPD (ZAN-BPD), and level of PTSD (PTSD-8) are used as interaction terms in the Cox proportional hazards regression models.

A secondary analysis of differences in compliance in filling out daily registrations between mobile phone and paper groups will use Wilcoxon rank sum to test the hypothesis of improved compliance in the active arm of the intervention. The problem of backfilling paper diary entries [57] cannot be easily controlled in the pen-and-paper version, but in the mobile phone condition, it will only be possible to back fill 2 days’ worth of entries, so clusters of 3-day fill-outs will signal backfilling. This bias in the study will be addressed in the interpretation of the results.

On an explorative level, time series data from daily data collection will be used to predict a binary classification of treatment in responders and nonresponders. In this analysis, the classification of responders and nonresponders will be based on the definitions provided by Jacobson et al [58] and and Schmitgen et al [59].

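### The 90% power claim treats each learned skill as independent, but the planned test is a frailty model on randomised patients, so the claim depends on an unstated frailty variance

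*Protocol article*

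**What the plan says.** The Power section of the protocol article plans 80 patients with equal allocation and expects mean times to learn a skill of "1.5 month (44 days) for mobile phone registration versus 2 months (60 days) for the control condition". For two-group testing at the 5% level with 90% power, it concludes that "we will need 437 events of learned skills in total to reject the null hypothesis". It adds that the calculation rests on the log-rank test.

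It then forecasts events. With 20% attrition, 64 patients remain and need about 7 skills each. A cautious forecast of 32 patients learning 16 skills gives 512 events, which the section calls sufficient. A more realistic forecast of 75% of patients learning 75% of skills gives 1188 events, which it says "will leave ample room to adjust for shared frailty".

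The Randomization section allocates individual patients 1:1. The second Statistical Analysis section, after Outcomes Collected, specifies Cox regression with multiple events per patient and states: "Significance tests are based on a frailty mixed effects approach". The Abstract also names a shared frailty model for the primary outcome.

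**The concern.** The sample size is expressed in learned skills, while treatment varies only between patients. If some patients learn faster than others whatever their arm, skills from one patient are correlated, and the precision of the treatment comparison is limited by the number of patients. The planned frailty test allows for this; the 437 count does not. The section treats surplus skills as the reserve for frailty, but extra skills from the same patients shrink only one of the two parts of the variance.

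At stake is how the result is read. A null primary result would be taken as coming from a trial with 90% power, when its power for the planned difference could be far lower.

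**Working it through.** **Inputs from the Power section.** Two-sided alpha .05 (the side is not stated, but only two-sided reproduces the figure); power .90; means 44 and 60 days; 80 patients, 64 after attrition; 437, 512 and 1188 events.

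**Assumptions.** Exponential learning times, so the hazard ratio is the ratio of means. Theta is the between-patient frailty variance; the article gives no value, so a range is shown. The patient is taken as the frailty unit, which is the natural reading of multiple events per patient but is not stated.

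**Step 1: reproduce 437.** ln(60/44) = 0.3102. Schoenfeld's formula with 1:1 allocation gives

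D = 4 × (1.960 + 1.2816)² / 0.3102² = 436.9, that is 437.

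No term allows for several events per patient.

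**Step 2: add patient frailty.** With D events from N patients, approximately

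Var(log HR) = 4/D + 4·theta/N,

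Power = Φ( 0.3102 / √Var − 1.960 ).

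The first term falls as skills accumulate. The second depends only on patients. The approximation ignores censoring, site effects and the interaction terms.

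Example with D = 1188, N = 64, theta = 0.25: Var = 0.00337 + 0.01563 = 0.01899, √Var = 0.1378, and 0.3102/0.1378 − 1.960 = 0.29, so power is 61%.

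| Events | Patients | theta 0.05 | 0.1 | 0.25 | 0.5 |
|---|---|---|---|---|---|
| 437 | 64 | 80% | 70% | 50% | 34% |
| 512 | 64 | 84% | 74% | 53% | 35% |
| 1188 | 64 | 97% | 88% | 61% | 38% |
| 1188 | 80 | 98% | 92% | 69% | 45% |

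**Step 3: largest theta that keeps 90%.** The variance must not exceed (0.3102/3.2416)² = 0.009155, so theta ≤ (0.009155 − 4/D) × N/4.

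| Events | Contributing patients | Largest theta |
|---|---|---|
| 437 | 64 | 0.00 |
| 512 | 32 / 64 / 80 | 0.01 / 0.02 / 0.03 |
| 1188 | 48 / 64 / 80 | 0.07 / 0.09 / 0.12 |
| unlimited | 64 / 80 | 0.15 / 0.18 |

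The rows with 32 and 48 patients apply if the event forecasts are met only by the patients they count.

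**Step 4: detectable ratio.** For 90% power at theta 0.25 with 64 patients and 1188 events, the ratio of means is exp(3.2416 × 0.1378) = 1.56, against the planned 60/44 = 1.36.

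**The case against.** The strongest reply is that the article does not ignore frailty. It names a frailty test, and it points to the 1188-event forecast as the reserve. That stands in part: moving from 437 to 1188 events raises the tolerable theta from 0 to about 0.09 with 64 patients. At theta 0.05 power is then about 97%.

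It is also fair to say that 64 is the pessimistic patient count. The analysis is by intention to treat, and patients who leave during follow-up may contribute skills first. With all 80 contributing, 1188 events keep 90% up to theta of about 0.12. This is an upper bound, and the fix should show both counts.

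Three stronger readings might be inferred, and the documents support none of them:

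- That 80 patients are too few at any plausible heterogeneity. The article gives no theta, so no value can be ruled out from it, and small values leave power above 90% at 1188 events.
- That the event forecasts themselves reveal a large theta, because they count only half or three quarters of the patients. They are forecasts of event totals and do not say that the other patients learn nothing. Counts of learned skills also vary with the number of skills started and time in therapy, so they do not measure heterogeneity in the time from starting to learning a skill.
- That the trial risks an inflated type I error. That would follow only if skills were tested as independent, and the article plans a frailty test.

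Finally, recruitment and follow-up were over by the dates in the Abstract, and the article also defends 80 as a realistic recruitment goal. This is why the remedy is a corrected statement and no change in size. It does not make the stated power right.

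**Conclusion.** The point holds in a conditional form. The 437 events and the 90% power belong to a log-rank test on independent skills, which is not the planned analysis. Under patient frailty, 90% has no reserve at 437 events; the claim that 512 events suffice fails once theta exceeds about 0.01 to 0.03; and the 1188-event forecast supports 90% only up to about 0.07 to 0.12. The last range corresponds to a between-patient standard deviation of the log learning rate of roughly 0.26 to 0.35 (the square roots of 0.07 and 0.12). The assertion of ample room for frailty is therefore unsupported by anything the article gives. It is not shown false, because theta is unknown. Above about 0.15 (64 patients) or 0.18 (80 patients), further skills cannot restore 90%.

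These figures rest on exponential times, the patient as frailty unit, and a variance approximation that ignores censoring, site effects and interactions. The planned test itself is not called into question.

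**What to change.** Keep 80 patients. In the Power section:

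- Describe 437 as the event count for independent events, and remove the unconditional claims of 90% power, of sufficiency at 512 events and of ample room for frailty.
- Give power under the planned frailty test over a stated range of theta, for example 0.05 to 0.5, informed by the pilot data, for 64 to 80 contributing patients.
- Give the detectable ratio alongside, for example about 1.56 for 90% power at theta 0.25, 64 patients and 1188 events.
- In the Statistical Analysis section, state that the patient is the frailty unit.

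The cost is one rewritten paragraph and a less favourable stated power. No patients are added and the primary analysis does not change.
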